### Monitoring of this project

A professional Project Management Committee (PMC) has been established in the CIAP, in which experts in statistics, neurosurgery, database management, and ethics are enrolled [14]. An inspection team has been established by the members of the PMC to ensure the smooth implementation of the research. The team will visit each clinical center regularly to promote the progress of this project. The first inspection will be conducted as soon as possible after screening the first patient. A CRO will be an internal part of this project to ensure the high quality of the data. The database and research materials will be censored on a regular basis by the CRO to ensure the authenticity, objectivity, accuracy and completeness of the data.

### Statistical methods

#### Sample size calculation

The sample size is calculated based on the following formula:$$ n = \frac{{u_{\alpha }^{2} p\left( {1 - p} \right)}}{{d^{2} }} $$

The annual rupture rate is expected to be 1% [9], the allowable error is d = 0.6%, the tests will be two-sided, with an α level of 0.05. It is calculated that 1173 subjects need to be enrolled in 1 year, and 4696 subjects are needed in 4 years. The expected drop-out rate is 5%. Drop-out is identified as enrolled patients who cannot be included in the primary analysis because, for example, they did not complete the follow-up in time or they lack key information.

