### Study design and methods

The China Intracranial Aneurysm Project (CIAP) is a prospective, observational registry study of the natural courses, risk factors for the onset and rupture, treatment methods, comorbidity management and other aspects of IAs. To the best of the authors’ knowledge, the CIAP, sponsored by Chinese Science and Technology Ministry and National Stroke Prevention Project Committee, is the largest ongoing project evaluating IAs in China; it currently includes 5 studies. The first study in the CIAP was designed to set up and manage a UIA database of 5000 individuals and calculate the annual rate of rupture of those aneurysms. The second study aimed to identify the risk factors for aneurysm rupture and develop a multidimensional predictive model for rupture. The third study was designed to explore the strategy of antithrombotic therapy in UIA patients complicated by ischemic cardiovascular/cerebrovascular diseases. The fourth study was designed to compare the therapeutic effects of intervention surgery and craniotomy surgery in the treatment of UIAs. The fifth study was designed to develop a standardized clinical pathway for early-stage cerebral hemorrhage caused by aneurysms [12, 13].

CIAP-1, intended to establish an open research platform and a nationwide UIA cohort, is the first and most fundamental task of the entire project. It is designed to achieve the following aims:Establish a nationwide public health and research platform administered by researchers, doctors, clinical center managers, Contract Research Organizations (CROs) and health management companies.Establish a nationwide prospective UIA cohort as a joint effort from 20 clinical centers.Clarify the natural history and annual rupture rate of UIAs in China.Identify the characteristics of people with intracranial aneurysms and look for possible causes of IAs.Screen for risk factors for UIA rupture and provide guidance to CIAP-2, which is designed to establish a multidimensional model to predict UIA rupture.

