### Statistical analysis

Statistical description of the clinical data.Continuous variables are expressed as the mean ± standard deviation and compared by one-way analysis of variance. Categorical variables are expressed as the quantity (rate) and compared with the Chi-square test. Continuous variables that do not conform to a normal distribution are expressed using the median and interquartile range and are compared by the Mann–Whitney nonparametric test. P < 0.05 is considered significant.Annual rupture rate calculation.The overall annual rupture rate of UIAs is the proportion of aneurysms that ruptured in one year, which will be calculated with the data from the 1-year assessment. When analyzing the rate in a specific population, a subgroup analysis will be performed.Assessment of influential factors.Multivariate regression analysis will be used to calculate the OR of high-risk factors for the development and rupture of aneurysms. The 95% confidence interval will also be calculated. The receiver operating characteristic curve (ROC) will be used to determine the cutoff value with the best sensitivity and specificity for the prediction of rupture.

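### The stated sample sizes of 1173 and 4696 do not follow from the printed formula with 5% drop-out, and the factor of 4 is unexplained

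*Protocol article*

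**What the plan says.** The Sample size calculation section of the protocol article prints the formula n = u²p(1−p)/d² and all its inputs:

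- Expected annual rupture rate: 1%.
- Precision target: "the allowable error is d = 0.6" per cent.
- Error level: "the tests will be two-sided, with an α level of 0.05".
- Attrition: "The expected drop-out rate is 5" per cent. It is defined as follows: "Drop-out is identified as enrolled patients who cannot be included in the primary analysis".

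The result is given as: "It is calculated that 1173 subjects need to be enrolled in 1 year, and 4696 subjects are needed in 4 years". The section does not say whether these numbers are before or after drop-out, or why the one-year number is taken four times.

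The Statistical analysis section defines the main estimate: "The overall annual rupture rate of UIAs is the proportion of aneurysms that ruptured in one year, which will be calculated with the data from" (cut short here; the source named is the visit at one year). It plans no separate rate for each enrolment year, but it does plan subgroup rates, regression for risk factors and a ROC cutoff. Study design and methods describes the first study's task as to "set up and manage a UIA database of 5000 individuals", and the Abstract expects more than 5000 patients.

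**The concern.** Formula, inputs and result stand in one paragraph, so a reader can check them, and they disagree. Nothing has to be looked up in a fuller document to see this, so it is not a matter of an article condensing a longer plan.

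The annual rupture rate is a main purpose of the study, and this paragraph is the only justification given for its size. As printed, it does not show which drop-out rate was assumed, whether 4696 is a number to enrol or a number to analyse, or what the precision target has to do with 4696 patients.

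**Working it through.** **1. Formula result.** With u = 1.96, p = 0.01 and d = 0.006 (all from Sample size calculation):

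n = 1.96² × 0.01 × 0.99 / 0.006² = 0.03803 / 0.000036 = 1056.44, so 1057 evaluable subjects.

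**2. Adding the stated 5%.** Drop-outs are defined as enrolled patients who are not in the primary analysis, so the inflation is n/(1 − 0.05):

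- 1056.44 / 0.95 = 1112.04, so 1113 enrolled. The cruder n × 1.05 gives 1109.3, so 1110.
- Four times: 4 × 1112.04 = 4448.2, so 4449.

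The printed 1173 is 11% above 1057 and 60 subjects above 1113.

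**3. What would give the printed figures.**

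| Reading | One year | Four years |
|---|---|---|
| Printed | 1173 | 4696 |
| Formula, no drop-out | 1057 | 4226 |
| Formula, 5% drop-out | 1113 | 4449 |
| Formula, 10% drop-out | 1173.8 | 4695.3, rounded up to 4696 |
| Printed figures taken as pre-drop-out, 5% added | 1173/0.95 = 1235 | 4696/0.95 = about 4943 |

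A 10% drop-out matches both printed numbers, but 10% appears nowhere in the article. Two other departures from the stated inputs come near 1173: u rounded to 2 with 5% drop-out (1158), and 5% applied twice (1171). Neither fits as closely. On the last row of the table, 5% was used, the total lands near the 5000 target, and only the base of 1173 is unexplained. The article does not settle which reading is right.

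**4. The factor of 4.** The formula sizes one proportion. With 1057 evaluable subjects the half-width is 1.96 × √(0.0099/1057) = 0.600 points, so the allowable error is already met for the single pooled 1-year rate. Nothing in the formula calls for four such samples.

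**5. Precision of the planned size.** The half-width for a 1% rate is 1.96 × √(0.0099/N), treating each patient as one independent unit:

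- 4696 enrolled, 5% lost: N = 0.95 × 4696 = 4461; half-width 0.292 points. The exact 95% interval at 45 ruptures is 0.74% to 1.35%.
- 5000 enrolled, 5% lost: N = 4750; half-width 0.283 points.

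The article does not say whether the 5% covers patients who leave because the aneurysm is treated. Observation ends at surgery (the follow-up section and the Discussion), and the Discussion describes over-treatment as serious. With total loss from 4696 assumed at 10%, 30% or 50%, N is 4226, 3287 or 2348, and the half-width is 0.300, 0.340 or 0.402 points. The allowable error would still be met until N fell to 1057, that is with 1 − 1057/4696 = 77% lost. This is about random error only, not about bias from selective treatment.

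**The case against.** The strongest reply is that no harm follows. Every discrepancy makes the sample larger than the formula needs, and the 0.6 points is a tolerance that a larger sample simply meets. That stands, and it limits the weight of the point.

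A second reply is that the larger number has a purpose. The article plans subgroup rates, stratified analysis and risk-factor regression. At 1%, 1057 patients would yield about 11 ruptures, against about 45 among 4461. This also stands in substance, and it is why the multiplication should be explained and not just struck out. But the sample size section does not give that reason; it presents 4696 as a result of the calculation.

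Several stronger readings are tempting and are not supported:

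- That a 10% drop-out was used and misreported as 5%. The match is close, but it is an inference; adding 5% to 4696 also leads to a figure near the stated target.
- That the article promises a final precision of ±0.6 points. It names an allowable error for sizing and makes no statement about the final interval.
- That 4 × 1173 = 4692 is a further error. 4696 is 4 × 1174, or 4695.3 rounded up; the gap is only rounding.
- That the study is too small. For the overall rate, the figures point the other way.

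**Conclusion.** The point holds as a fault in the justification. The printed formula and inputs give 1057 evaluable and 1113 enrolled at 5% drop-out; the stated 1173 is about 5% above 1113, and 4696 is likewise above 4449. The origin of the printed figures is not stated. The factor of 4 has no basis in the formula, since the main estimate is one pooled 1-year rate.

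The figure of about ±0.29 points for the planned size rests on a true rate near 1%, one independent unit per patient and no more than 5% lost. The rate is defined per aneurysm and patients with multiple aneurysms are enrolled, so the first two of these simplifications follow the article's own formula and not its stated estimate exactly. The interval widens if patients leaving through treatment add to the loss. This should be corrected, but it does not put the study's size or its main estimate in doubt.

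**What to change.** Rewrite the paragraph in Sample size calculation:

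1. Give the formula result: 1057 evaluable subjects.
2. State the one drop-out rate actually used and the enrolled number that follows: 1113 at 5%, or 1174 at 10%. Only the sponsor can say which was meant. Say whether patients who leave through treatment are counted in it.
3. For the total of about 4700 to 5000, do one of two things. Give the real reason, for example subgroup rates and risk-factor regression, if that is what it was. Or present the number as a precision statement: about ±0.29 points for a 1% rate with 4461 evaluable, with the assumptions of one independent unit per patient and at most 5% lost, and a note that further loss through treatment widens the interval.
4. Say whether 4696 is before or after drop-out, and align it with the 5000 in the Abstract and in Study design and methods.

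The cost is one reworded paragraph. Enrolment, data collection and analysis do not change.

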### Statistical analysis

Statistical description of the clinical data.Continuous variables are expressed as the mean ± standard deviation and compared by one-way analysis of variance. Categorical variables are expressed as the quantity (rate) and compared with the Chi-square test. Continuous variables that do not conform to a normal distribution are expressed using the median and interquartile range and are compared by the Mann–Whitney nonparametric test. P < 0.05 is considered significant.Annual rupture rate calculation.The overall annual rupture rate of UIAs is the proportion of aneurysms that ruptured in one year, which will be calculated with the data from the 1-year assessment. When analyzing the rate in a specific population, a subgroup analysis will be performed.Assessment of influential factors.Multivariate regression analysis will be used to calculate the OR of high-risk factors for the development and rupture of aneurysms. The 95% confidence interval will also be calculated. The receiver operating characteristic curve (ROC) will be used to determine the cutoff value with the best sensitivity and specificity for the prediction of rupture.

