### Measures to reduce bias

*Control of selection bias* This is a nationwide population-based study. Twenty centers selected from different regions of China are involved in this study. The status of diagnosis and treatment in different regions of China will be investigated in this study and will be involved in the final analysis. In addition, the patients in each center will be screened consecutively according to the selection criteria.

*Control of information bias* Blinding is being adopted in this study. The clinical research associates (CRAs) will be blinded to the study design. The statistical analysis will also be conducted blindly.

A standardized training program will be created and implemented to ensure that all of the work is undertaken by well-trained CRAs and CRCs.

The double-check process will be implemented in the process of data collection. The quality of the data will be evaluated again before analysis. Unqualified data will be corrected if possible or will be removed if the information about its accuracy is not available. The impact of missing information will be fully considered and will be subject to special analysis.

Regularly communicating with the patients will help improve the quality of the follow-up. The CRAs will call the patients on a regular basis. Furthermore, mobile applications, such as Wechat (an instant messaging and social media application), will be used to establish effective communication channels. In the case of a nonresponding patient, the CRA will try to contact the patient again several days later.

*Control of confounding factors* As many potential confounding factors as possible will be identified. Considering that this is an observational study, overly strict selection criteria are not used.

The design and implementation of this study are guided by statistical experts. Statistical methods such as standardized rate, stratified analysis, multivariate logistic regression analysis and propensity score matching will be adopted to identify the influential variables. These influential variables will be taken into consideration when calculating the annual rupture rate and when establishing the multifactor analysis model in CIAP-2.

Subgroup analyses and a case–control study design will be used when calculating the rupture rate in specific populations. The selection criteria for the exposure group and the control group will be set reasonably, and multiple groups of controls will be used if necessary.

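### The precision formula and the named analyses treat patients from 20 centres as independent; if rupture rates differ between centres, the interval for the rate is too narrow and tests of centre-level factors are anti-conservative

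*Protocol article*

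**What the plan says.** Measures to reduce bias states: "Twenty centers selected from different regions of China are involved in this study". Participating center qualification names four regions and holds that the cohort can stand for the regional and national population. The bias section adds "The status of diagnosis and treatment in different regions of China will be investigated in this study" and says that this will enter the final analysis.

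Sample size calculation uses n = u²p(1−p)/d² with an expected annual rupture rate of 1%; "the allowable error is d = 0.6%, the tests will be two-sided, with an α level of 0.05". It reports 1173 subjects for one year and 4696 for four years, with 5% drop-out. There is no design-effect term.

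Statistical analysis defines the annual rupture rate as a one-year proportion. Under description of the clinical data it says "Categorical variables are expressed as the quantity (rate) and compared with the Chi-square test". For influential factors it names multivariate regression, with odds ratios and 95% confidence intervals. Measures to reduce bias adds: "Statistical methods such as standardized rate, stratified analysis, multivariate logistic regression analysis and propensity score matching will be adopted". The variables found this way feed into the rate calculation and the CIAP-2 model.

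No section gives centre a place in a variance or a model. None says that centre will be ignored.

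**The concern.** Patients within a centre share referral patterns, case mix, treatment policy and access to care. When the result is meant for China rather than for these 20 hospitals, variation between centres is part of the sampling error. A formula that counts every patient as a separate unit leaves it out.

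The article gives reasons to expect such variation. It plans to study regional differences in diagnosis and treatment, and its Discussion describes poor access in remote areas and serious over-treatment.

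Two results are exposed. One is the interval around the annual rupture rate, a main purpose of the study. The other is any test of region or local care pattern. These are properties of the centre, so they have about 20 independent units rather than about 4700. Stratifying by region leaves the variation between centres within a region where it was. A centre-level variable wrongly found influential would pass into the rate calculation and into CIAP-2.

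**Working it through.** **1. The plan's own figure.** With u = 1.96, p = 0.01 and d = 0.006: n = 1.96² × 0.01 × 0.99 / 0.006² = 1056.4. Dividing by 0.95 for the stated 5% drop-out gives 1112, not 1173. Dividing by 0.90 gives 1173.8, and 4 × 1174 = 4696. The printed figures therefore match 10% drop-out, which is a separate inconsistency. Neither figure contains an allowance for clustering.

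**2. Half-width under independence.** At N = 4696: 1.96 × √(0.0099/4696) = 0.285 percentage points.

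**3. Allowing for centre.** Twenty equal centres give m = 4696/20 = 234.8 patients each. The ICC is an assumption. The formulas are:
- design effect: DE = 1 + (m − 1) × ICC
- SD of centre rates: √(ICC × 0.0099)
- true half-width: 0.285 × √DE
- coverage of the naive 95% interval: 2Φ(1.96/√DE) − 1
- false-positive rate of a patient-level 3-df test across four regions: P(χ²₃ > 7.815/DE)

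| ICC | SD of centre rates (points) | DE | True half-width (points) | Naive coverage | False positives, 4 regions |
|---|---|---|---|---|---|
| 0 | 0 | 1.00 | 0.285 | 95% | 5% |
| 0.001 | 0.31 | 1.23 | 0.316 | 92% | 10% |
| 0.002 | 0.44 | 1.47 | 0.345 | 89% | 15% |

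An ICC of 0.005 would give 82% and 31%. It implies a centre SD of 0.70 points around a mean of 1%, a very large difference between centres, so it should carry little weight. Higher values should carry less.

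**4. Simulation.** Beta-binomial data (20 centres of 235, four regions of five centres, 40,000 runs) at ICC 0, 0.001 and 0.002 gave:
- naive coverage 94.6%, 91.6% and 88.7%
- region-test false positives 4.9%, 9.3% and 14.7%
- for a factor balanced within centres, false positives 5.0%, 5.0% and 5.1%

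**5. The allowable error.** The 0.6% is lost at N = 4696 only when DE exceeds 0.006² × 4696/(1.96² × 0.0099) = 4.45, which is an ICC of (4.45 − 1)/233.8 ≈ 0.015. If the 1173 subjects were analysed alone (m about 59), the half-width would be 0.569 points under independence and 0.601 at ICC 0.002, a bare miss.

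**6. The remedy.** In a second simulation (4460 evaluable patients after 5% drop-out, 4000 runs), a cluster-robust logit interval with a t reference on 19 df covered 95.0%, 96.0% and 95.1% at ICC 0, 0.001 and 0.002. A centre-level analysis of variance across regions had 4.9%, 5.1% and 4.8% false positives.

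**The case against.** The strongest reply is that this is silence in a condensed article. Variance estimation usually sits in the analysis plan, which is not shown. The list of methods in Measures to reduce bias is explicitly open, and regression does not exclude a centre term. This softens the point to a clarification of the analysis. It does not remove it, because the precision basis is printed here, in a form that holds only without between-centre variation.

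Several stronger readings do not stand:
- A reader might infer that a patient-level Chi-square test of rupture across regions is planned. The Chi-square sentence belongs to the description of clinical data, and no such test is stated. The 10% to 15% shows what a patient-level test would do.
- A reader might infer that a wrong interval method is fixed for the rate. The 95% interval in Statistical analysis is stated for the odds ratios; none is specified for the rate.
- A reader might take the Discussion's contrast by size as proof of centre differences. It compares patients: five-year rupture of 40–50% above 25 mm against 0–2.5% below 7 mm, or crudely 8–10% against 0–0.5% a year. To reach ICC 0.002 from that contrast alone, the share of aneurysms above 25 mm would have to vary between centres with an SD of about 0.445/8.75 = 5 percentage points. The article gives no case-mix figures.

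It is also fair that the centres were selected rather than drawn at random, so treating them as random is a modelling choice. The claim to represent the regional and national population is what calls for it.

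**Conclusion.** The point holds conditionally, as a cheap improvement. The printed formula and the named analyses in their plain form assume independent patients, while the inference claimed goes beyond the 20 centres. If centres differ modestly (ICC 0.001 to 0.002), a nominal 95% interval for the rate covers about 92% to 89%, and a patient-level test of a regional factor rejects falsely about 10% to 15% of the time.

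This rests on an assumed ICC and on equal centre sizes. Unequal sizes make it somewhat worse: with a lognormal spread (sigma 0.6), simulated coverage at ICC 0.002 fell from 89.6% to 87.4%.

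It might be inferred that the interval is certainly too narrow, that the sample is too small, or that every risk-factor test is compromised. The documents support none of these. They give no ICC, the 0.6% target survives at 4696 up to an ICC of about 0.015, and patient-level factors balanced within centres keep their 5% error rate.

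**What to change.** In Statistical analysis, state that:
- the interval for the annual rupture rate uses a variance clustered on enrolling centre, for example cluster-robust on the logit scale with a t reference on 19 df
- the regression accounts for centre, by cluster-robust or GEE standard errors with a small-sample correction or by a random centre effect, and is kept simple, because only about 0.01 × 4696 = 47 ruptures are expected, or 2.3 per centre (the regression option was not simulated here)
- region and other centre-level factors are tested against between-centre variation.

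Patients registered through the Stroke Prevention Project Committee need a stated centre for this purpose.

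In Sample size calculation, state that d = 0.6% assumes no between-centre variation, and give the half-width over a small range of ICCs (0.285, 0.316 and 0.345 points at ICC 0, 0.001 and 0.002 for 4696 patients).

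The cost is wording. Data are already collected by centre and no enrolment is added. The downside is a somewhat wider interval and less apparent power for regional comparisons. If centres do not differ, little is lost: simulated coverage of the clustered interval was 95.0% at ICC 0.

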### Recruitment of participants

Patients will be enrolled consecutively in all of the clinical centers and through China’s Stroke Prevention Project Committee. Patients with UIAs will be enrolled when they first visit the clinical center or are registered by the Stroke Prevention Project Committee. Patients with multiple aneurysms will also be enrolled when at least one aneurysm remains untreated. The patients will be selected according to the following selection criteria.

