An observational design was chosen for this study, in which the diagnosis and treatment of disease will not be affected. Compared with an interventional study, more patients with different characteristics can be enrolled in a real-world study that has lower internal validity but superior external validity. The results of the real-world study better represent the current status of the diagnosis and treatment of diseases. At the same time, the study can be implemented for a long period of time, include a large sample size, and provide benefits for less of an investment. Furthermore, the conclusions drawn from the study might be more easily extrapolated to and more useful in clinical practice. Lastly, registration studies are safer for the participants [15, 16]. Despite the shortcomings [17], a real-world study is still the most suitable design for this study.

The UIA research platform will be established in this study based on multicenter cooperation and will take advantage of the EDC system. There are 3 cohorts in this platform: the Cohort of Unruptured Aneurysm without Treatment (CIAP-1, CIAP-2, CIAP-3), Cohort of Unruptured Aneurysm with Treatment (CIAP-4), and Cohort of Ruptured Aneurysm (CIAP-5). The relationships among these five studies have been clearly described in the protocol of CIAP-2 and CIAP-4 [12, 13]. The patients in this study (CIAP-1) will be transferred to the cohort in CIAP-5 if the IA ruptures. They will be transferred to the cohort in CIAP-4 if the IA is surgically treated. Under these conditions, observation will be discontinued for this study. The patients in CIAP-1 will also be enrolled in CIAP-2/CIAP-3 if they meet the additional selection criteria (Figs. 1, 2).

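### The rupture rate is counted per aneurysm but the study is sized per patient, and the exit rule makes no provision for a patient's remaining untreated aneurysms

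*Protocol article*

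**What the plan says.** All of the following is in the protocol article.

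- **Unit of the result.** Statistical analysis: the overall annual rate is "the proportion of aneurysms that ruptured in one year", calculated from the 1-year assessment.
- **Unit of the sample size.** Sample size calculation: "It is calculated that 1173 subjects need to be enrolled in 1 year, and 4696 subjects are needed in 4 years". The inputs are "The annual rupture rate is expected to be 1% [9], the allowable error is d = 0.6" (percent), and "the tests will be two-sided, with an α level of 0.05". Drop-out (5%) is defined as patients who cannot enter the primary analysis. The section does not say whether the 1% is per aneurysm or per patient, and does not mention the number of aneurysms per patient.
- **Who is enrolled.** Recruitment of participants: "Patients with multiple aneurysms will also be enrolled when at least one aneurysm remains untreated".
- **When observation ends.** The plan and methods of follow-up keeps a patient for at least a year unless the aneurysm (singular) ruptures or is operated on. The Discussion moves the patient to CIAP-5 if the aneurysm ruptures. For treatment it says: "They will be transferred to the cohort in CIAP-4 if the IA is surgically treated". In both cases CIAP-1 observation stops.
- **The aim.** Study design and methods describes the first study as a database of 5000 individuals and the annual rupture rate of their aneurysms, so both units appear in one sentence.

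**The concern.** The two units agree only if every patient has one aneurysm, and the recruitment rule expressly allows more. A per-aneurysm and a per-patient rate are then different numbers, and the plan does not say to which of them its 1% and 0.6% belong.

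The exit wording makes this worse in two ways. A patient who leaves at rupture contributes at most one rupture (simultaneous ruptures apart), while all of that patient's aneurysms can enter the denominator. And a patient with one treated and one untreated aneurysm is eligible if the treatment came before enrolment, but leaves if it comes afterwards, although the untreated aneurysm is still at risk. A simple one-year proportion has no place for an aneurysm whose patient left early: it must be either counted as not ruptured or dropped.

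The annual rupture rate is a main purpose of the study. The Discussion itself describes over-treatment of unruptured aneurysms as a serious problem in China, so exits through treatment should be expected.

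**Working it through.** **1. The plan's own figure.** n = u²p(1−p)/d² with u = 1.96, p = 0.01, d = 0.006:

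1.96² × 0.01 × 0.99 / 0.006² = 1056.4, i.e. 1057 subjects.

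With the stated 5% drop-out, 1056.4/0.95 gives 1113. The printed 1173 is not reproduced. A 10% drop-out fits: 1056.4/0.90 = 1173.8, and 4 × 1174 = 4696. That is a separate matter and does not come from the unit conflict.

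**2. How far apart the two rates are.** The article does not give the mean number of aneurysms per patient, m. Assume m = 1.1 to 1.5.

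- If 1% is per aneurysm, the per-patient rate is about 1% × m = 1.1% to 1.5%.
- If 1% is per patient, the per-aneurysm rate is about 1%/m = 0.91% to 0.67%.

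**3. Untreated aneurysms lost through exit after treatment.** Assume that a share f of patients have two aneurysms (the rest one) and that a share t of these have one treated within the year. The lost share of all aneurysms is f·t/(1+f). Numbers are for 4696 × 0.95 ≈ 4461 patients.

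| f | t | share lost | aneurysms lost |
|---|---|---|---|
| 10% | 10% | 0.01/1.1 = 0.9% | 45 |
| 20% | 30% | 0.06/1.2 = 5.0% | 268 |
| 30% | 50% | 0.15/1.3 = 11.5% | 669 |

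These are aneurysms with incomplete follow-up. The share of time at risk that is lost is smaller, because each is observed until its patient leaves. As an outer bound, suppose every aneurysm has a 1% risk, the lost ones stay in the denominator and none of their ruptures is counted. The recorded rate is then 1% × (1 − 0.009) = 0.991% down to 1% × (1 − 0.115) = 0.885%. If they are dropped instead, the rate is undistorted only if they carry the same risk as those retained.

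**4. Precision.** Half-width = 1.96 × √(p(1−p)·DE/(4461·m)), with DE = 1 + (m* − 1)·ICC. Here m* is the size-weighted mean number of aneurysms per patient (one or two each).

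- Patients as the unit: 1.96 × √(0.0099/4461) = 0.29 points.
- m = 1.5, ICC = 0: 0.24 points (the narrowest).
- m = 1.3, ICC = 1 (m* = 1.9/1.3 = 1.46): 0.31 points (the widest).

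All are well inside d = 0.6.

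**5. Clustering under the exit rule as worded.** If a patient leaves at rupture, ruptures within a patient are mutually exclusive. For two aneurysms at 1% each, the variance of the patient's count is 0.02 × 0.98 = 0.0196, against 0.02 × 0.99 = 0.0198 if they are treated as independent. The naive variance is then not too small.

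**The case against.** The strongest reply is that this needs only a clarifying sentence. Subjects are what a registry enrols, each has at least one untreated aneurysm, and sizing in subjects is no statistical error in itself. The follow-up and Discussion sections speak of one aneurysm and do not address several. The Discussion also refers to companion protocols and flow charts that are not shown. Variance methods are commonly left to an analysis plan.

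Much of this stands, and it rules out several stronger readings that a reader might infer:

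- **The study is too small.** Not supported; see the half-widths above.
- **The unit conflict shifts the rate by as much as the planned error.** At m = 1.4, 1%/1.4 = 0.71%, a shift of 0.29 points, which happens to equal the pooled half-width. But the planned error is 0.6%. Nothing says that the planning 1% is per patient, and the Discussion words the source figure (0.95%) as a rate of unruptured aneurysms, which fits a per-aneurysm reading.
- **Confidence intervals and standard errors are too narrow.** Not shown. The article does not say that aneurysms are treated as independent, and exit at rupture rules out positive correlation in counted ruptures. Full correlation would inflate the standard error by √1.18 = 1.09 to √1.57 = 1.25 for m = 1.1 to 1.4, but nothing supports full correlation.
- **Remaining aneurysms are dropped by rule.** This follows from the plain wording; it is not stated.
- **The per-patient rate must be primary.** That is a preference. The stated aim is the rupture rate of the aneurysms.

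What the reply does not remove is the printed difference in units, or the mismatch between an enrolment rule that admits partly treated patients and an exit rule written for one aneurysm.

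**Conclusion.** The point holds as a conflict within the article. The rate is per aneurysm, the sample size and drop-out are per subject, the unit of the 1% is not stated, and eligibility guarantees that the two can differ. Read plainly, the follow-up and exit rules leave a patient's remaining untreated aneurysms unobserved, which does not fit the enrolment rule.

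The damage is to what is estimated, namely the denominator and the time at risk. Its size is about 0.9-11.5% of aneurysms lost while untreated. This rests on assumed shares of patients with two aneurysms (10-30%) and of those treated within the year (10-50%), neither of which the article gives. The effect on precision is small. The change is worth making because it is cheap and protects the main estimate.

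**What to change.** - State the unit of the 1%, and use one unit for the sample size and the rate.
- If the unit stays the aneurysm, replace the simple one-year proportion with ruptures per aneurysm-year. End time at risk separately for each aneurysm, and use a patient-clustered variance for the rate and for aneurysm-level regressions.
- Report first rupture per patient alongside.
- Reconcile Recruitment of participants, The plan and methods of follow-up and the Discussion by stating whether untreated aneurysms that remain after another is treated or ruptures stay under CIAP-1 observation.

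The cost is analysis wording, continued contact with a subset of patients, and possibly a slightly wider per-aneurysm interval. The number and location of aneurysms are already among the imaging data to be collected.
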